### Materials/laboratory analyses

Non-invasive screening options (i.e., self-collected vaginal swabs, avoiding speculum examination) have been developed and validated in the last decade [22] and have high acceptability [23]. Participants will use commercially available Conforme aux Exigences (CE)-marketed Aptima Multitest swab specimen collection kits (Hologic, San Diego, CA, USA) to provide their vaginal samples at months 0, 6, 12 and 18. The flow of the trial is depicted in Fig. 3.

**Fig. 3 Fig3:**
[figure not shown]
Sample flow of the i-Predict trial

After sampling, the kit will be returned to the CNR (Bordeaux, France) in a pre-addressed, prepaid envelope. At the CNR, samples will be recorded. All samples will be analysed using a commercially available, CE-marketed, transcription-mediated amplification assay (Aptima Combo 2 CT/NG; Hologic) on the automated Panther instrument (Hologic), which performs well on self-collected vaginal swabs [24]. In the intervention group, samples will be analysed upon arrival. Analysis will be deferred for the control group to after the 18-month study period, and the samples will be stored at − 80 °C immediately after being received.

To determine whether a Ct infection is persistent or new, typing methods developed in the CNR will be applied, enabling high-resolution molecular epidemiological characterisation of Ct genovars D to K: *omp1* gene PCR-restriction fragment length polymorphism [25] or *omp1* gene sequencing, followed by multiple loci variable-number tandem repeat analysis [26] in case the same genovar is identified in two samples from the same subject. The CNR will perform DNA extraction from vaginal swabs and transfer the prepared samples to the immunogenetics laboratory for SNP biomarker analyses. These will be performed using a set of over 50 SNPs already identified and validated to be predictive of tubal factor infertility susceptibility [16].

### Sample size

The cumulative number of PID cases (from baseline to up to 18 months) was estimated in each group, assuming no natural clearance of Ct infection in the absence of treatment, because Ct infection is mostly asymptomatic and the follow-up relatively short in comparison to infection duration, which is most likely > 1 year [13]; 100% treatment efficacy to clear Ct and PID; and an average 3-month lag between Ct acquisition and PID onset [27, 28]. The same number of Ct-infected and PID cases is expected in the two groups at baseline, assuming that observed Ct infections at baseline have been prevalent for an average of 9 months (hence a PID cumulative incidence over 6 months).

Assuming a 5% yearly incidence of Ct infection [14] and a 1% yearly incidence of PID among Ct-negative young women, we calculated that a sample size of 2000 participants in each group would allow us to detect a 0.54 relative risk (RR) between the intervention and control groups with a 5% one-sided type I error rate and 80% power, assuming either 5% Ct prevalence at baseline [12] and 12% PID incidence among Ct-positive participants or 7% Ct prevalence at baseline [29] and 10% PID incidence among Ct-positive participants [12], and accounting for a 10% attrition rate. Therefore, 4000 sexually experienced female students aged 18 to 24 years participating in the i-Share French student cohort will be enrolled.

### Statistical analyses

For the primary analysis, we will calculate the cumulative incidences of developing PID over 24 months in both groups and estimate the RR of developing PID as the ratio of these incidences (intention-to-treat analysis). We will consider probable and confirmed PID together first and conduct confirmatory analysis restricted to confirmed PID only.

For comparison with previous trials, we will further stratify our RR analysis on baseline status of Ct infection. We will also conduct an exploratory Cox regression analysis to adjust the RR of developing PID for other baseline characteristics of the participants. Missing data imputation will be considered for participants’ characteristics (excluding Ct and PID status) when missing values exceed 10%.

As secondary analyses, we will determine the following:Annual incidence of Ct infection based on the first recorded Ct infection among participants Ct-negative at baseline in both groupsAmong participants in the control group with incident Ct infection (participants Ct-negative at baseline), proportions (and 95% CIs) of Ct infections with spontaneous resolution and of Ct infections evolving towards PID; estimation of the duration of Ct infection (from Ct detection to clearance) and time to develop PID (time between incident Ct infection and incident PID, defined as from 3 months before Ct detection because time windows correspond to 6 months, to the onset of PID symptoms)Among participants in both groups who have cleared Ct infection at least once, incidence of Ct reinfection and comparison between the treated (intervention) and untreated (control) groupsAmong participants in the control group, exploratory logistic regression to assess whether 50 immunogenetic biomarkers can predict Ct persistence and occurrence of PID

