#### Final visit

The final visit will take place between months 18 and 24 (depending on enrolment date to avoid the possibility that the final visit takes place during university summer break) and will include an extensive clinical examination by a gynaecologist for signs suggestive of PID and, if indicated, pelvic ultrasound. The gynaecologist will have access to chlamydia test results for both groups. For participants in the control group, the gynaecologist will review Ct results throughout the course of the study and decide whether the participant should get treatment based on these results. Final visits will take place at the hospital gynaecology department in geographical proximity to the recruiting universities: Poissy/Saint-Germain-en-Laye Hospital, Nice L’Archet Hospital, Paris Cochin Hospital and Bordeaux Pellegrin Hospital.

In the case where participants do not complete follow-up, attempts will be made to obtain information on the reasons for dropout. The last contact date will be recorded. To compensate participants for the time dedicated to the study, financial compensation will be given at the initial visit and at the final visit.

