### Outcomes

#### Primary endpoint

The primary endpoint measure is the cumulative incidence of first PID over 24 months in the intervention group (immediate testing and treatment) and in the control group following current screening recommendations (deferred testing). PID comprises a spectrum of inflammatory disorders of the female upper genital tract, including endometritis (inflammation of the uterine lining), salpingitis (inflammation of one or both fallopian tubes), tubo-ovarian abscess and pelvic peritonitis.

For the purpose of this study, the definition of PID is as follows [20]:
*Probable PID:* Clinical diagnosis of PID (pelvic pain, cervical motion tenderness, uterine or adnexal tenderness)
*Confirmed PID:* Clinical diagnosis of PID and one of the following criteria: laparoscopic abnormalities consistent with PID, endometrial biopsy with histopathologic evidence of endometritis, pelvic ultrasound showing thickened tubal wall (>8 mm), tubal fringes or free pelvic fluid

Data on symptoms reported by the participants and collected through medical records, as well as data collected at the final visit, will be reviewed by two independent experts blinded to group allocation (intervention or control) and to Ct infection status to classify the outcome status (no PID, probable PID or confirmed PID).

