## Trial status

The first enrolment date was January 10, 2017. The estimated last enrolment date will be in June 2019. The estimated follow-up completion date is January 2021. The estimated primary analysis completion date is October 2021.

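### The primary endpoint is 24-month PID incidence, but follow-up ends between months 18 and 24 and the sample size counts cases to month 18, so the plan has no single horizon that its follow-up supports

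*Protocol article*

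**What the plan says.** All places are in the protocol article.

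- **24 months.** Primary endpoint: "The primary endpoint measure is the cumulative incidence of first PID over 24 months". Main objective has the same horizon. Statistical analyses: "we will calculate the cumulative incidences of developing PID over 24 months in both groups", and then "estimate the RR of developing PID as the ratio of these incidences (intention-to-treat analysis". Design/setting and the Discussion (Expected results) also describe a 24-month trial and follow-up.
- **18 to 24 months.** Final visit: "The final visit will take place between months 18 and 24", with the timing set by enrolment date so as to avoid the summer break. No later assessment is described.
- **18 months.** Sample size: "The cumulative number of PID cases (from baseline to up to 18 months) was estimated in each group". Control group speaks of an 18-month study period, and the last swab is at month 18 (Follow-up).
- **Calendar.** Trial status: "The estimated last enrolment date will be in June 2019. The estimated follow-up completion date is January 2021".

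The only time-to-event method named is an "exploratory Cox regression analysis to adjust the RR of developing PID for other baseline characteristics". Imputation is considered for participant characteristics but not for PID status. The date of last contact is recorded for women who drop out (Final visit).

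**The concern.** A cumulative incidence has meaning only with a time attached. Here the objective, endpoint and analysis attach 24 months, the follow-up attaches a range, and the sample size attaches 18 months. If the observed proportions are reported as 24-month risks, they mix risks over 18 to 24 months and come out too low. The trial is meant to inform French screening recommendations, where the absolute risk of PID over a defined period matters. An unsettled horizon also leaves three candidates for the primary result (month 18, month 24, or through the final visit), and the choice could be made after the data are seen.

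**Working it through.** **1. Calendar.** From 30 June 2019 to 1 January 2021 is 18.1 months; from 1 June 2019 to 31 January 2021 is 20.0 months. The last entrants thus have about 19 months. A woman enrolled after January 2019 cannot reach month 24 by January 2021. Enrolment from 10 January 2017 to 30 June 2019 lasts 29.6 months, so under even accrual (an assumption) about 5/29.6 = 17% are in that position.

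**2. The plan's own figure.** The arm risks are not printed, so they are rebuilt from the Sample size inputs: Ct incidence 5% a year, PID 1% a year in Ct-negative women, no clearance, fully effective treatment, a 3-month lag, and either prevalence 5% with PID 12% or prevalence 7% with PID 10% in Ct-positive women. I read the 12% and 10% as yearly, which the article does not state. I use 6-month steps with infection at mid-step, so that after the lag PID risk starts at the next test, and I leave out PID already present at baseline.

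Control risk at 18 months = prevalent infections + incident infections + background.

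- Scenario 1: 0.05×0.12×1.5 + 0.95×0.025×0.12×(1.0+0.5) + 0.95×0.01×1.5 = 0.0090 + 0.0043 + 0.0143 = 2.75%.
- Scenario 2: 0.0105 + 0.0035 + 0.0140 = 2.79%.
- Intervention, both scenarios: 0.01×1.5 = 1.50%.

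The RRs are 0.545 and 0.537, against the stated 0.54.

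Sample size, one-sided 5% and 80% power: n = [1.645√(2p̄q̄) + 0.842√(p₁q₁+p₂q₂)]²/(p₁−p₂)² = 1640 in scenario 1. With the continuity correction, (n/4)[1+√(1+4/(n(p₁−p₂)))]² = 1796, and 1796/0.9 = 1996 per arm. Scenario 2 gives 1551, 1702 and 1892. The stated 2000 is reproduced at 18 months.

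**3. The same model at 24 months.** Scenario 1 control: 0.0120 + 0.95×0.025×0.12×(1.5+1.0+0.5) + 0.0190 = 3.96%. Scenario 2: 0.0140 + 0.0070 + 0.0186 = 3.96%. Intervention: 2.00%. The RRs are 0.506 and 0.505. The required size is 1149 and 1147 per arm, and power with 1800 evaluable per arm (2000×0.9) is about 96.5%.

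**4. A continuous-time version of the same inputs.** With T in years, control = prevalence×r×T + (1−prevalence)×0.05×r×(T−0.25)²/2 + (1−prevalence)×0.01×T, where r is yearly PID incidence in infected women. Intervention = 0.01×T + (1−prevalence)×0.05×r×0.03125 for each 6-month interval, where 0.03125 = 0.25²/2 is the exposure left between lag and next test.

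| Scenario | Horizon | Control | Intervention | RR |
|---|---|---|---|---|
| 1 | 18 months | 2.77% | 1.55% | 0.561 |
| 1 | 24 months | 3.97% | 2.07% | 0.521 |
| 2 | 18 months | 2.81% | 1.54% | 0.550 |
| 2 | 24 months | 3.97% | 2.06% | 0.518 |

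**5. Understatement of absolute risk by a simple proportion called 24-month risk.**

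- All women stop at month 18: 2.75/3.96 = 0.69 to 0.70, about 30% too low.
- Final visits evenly spread over months 18–24, infection model: about the midpoint, (2.75+3.96)/2 = 3.36%, and 3.36/3.96 = 0.85, about 15% too low.
- Evenly spread, constant hazard, illustrative 24-month risk 2.50%: 2.19%, and 2.19/2.50 = 0.88, about 12% too low.

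**6. Effect on the ratio.** With proportional hazards and equal follow-up by arm, the RR is 0.543 at 24 months and 0.543 for the even spread. In the 6-month model the spread gives 1.75/3.36 = 0.52, between the 18- and 24-month values. Only unequal follow-up would distort it much: mean follow-up of 20 against 22 months would turn 0.54 into about 0.54×20/22 = 0.49 or 0.54×22/20 = 0.59. That difference is purely illustrative.

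**7. Sensitivity of the reconstruction.** Other variants count PID present at baseline or remove newly infected women from the Ct-negative pool. One of them also gives an RR near 0.54 at 24 months (0.541), so the RR alone does not identify the horizon. The size does: with the continuity correction and attrition, every 24-month variant needs 1147 to 1588 per arm, all below 2000.

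**The case against.** The article never says that the ratio is crude. A reader might infer a plain ratio of proportions, with dropouts either removed or counted as PID-free because PID status is not imputed. The text does not support that. A cumulative incidence can be estimated with censoring, which needs no imputation, and the last-contact date and the planned Cox model suggest that follow-up times will be available. The choice of estimator may properly sit in an analysis plan not shown. This part of the objection stands.

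The comparison between arms is also largely protected. Final-visit timing follows enrolment date, and allocation is 1:1 within university, so timing should balance. The Trial status dates are estimates, and 19 months lies inside the 18–24 window. Two years of enrolment per centre (Initial visit), counted from January 2017, would even allow 24 months by January 2021, although Trial status gives June 2019. These points stand too.

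They do not remove the conflict. No choice of estimator reconciles a 24-month endpoint with a final visit from month 18 and a sample size to month 18. If visits spread evenly, the share of completers still under observation at month t is (24−t)/6: one half at month 21, one sixth at month 23 and none beyond month 24. A censored 24-month estimate would rest on few women at its end.

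**Conclusion.** The point holds as an inconsistency in the primary horizon that affects the absolute risks. A simple proportion labelled as 24-month risk would be about 12–15% too low with evenly spread visits; about 30% is the ceiling, reached only if every woman stopped at month 18. These sizes rest on reading the assumed PID incidence in infected women as yearly, on rebuilt arm risks, and on the stated visit patterns.

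Two stronger readings are not supported. One is that the RR or its test is invalid: with balanced visit timing the bias is small. The RR does depend on the horizon under the protocol's infection model (about 0.54–0.56 at 18 months, 0.51–0.52 at 24), so the horizon must be named. The other is that the trial is underpowered because the sample size used 18 months: that basis is conservative, and the variants of the 6-month model put 24-month power with 1800 evaluable per arm at about 90–97%.

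**What to change.** Reconcile Main objective, Final visit, Primary endpoint, Sample size, Statistical analyses and Trial status to one horizon that the follow-up supports. Enrolment began in January 2017, so the change should be dated and made before outcomes by arm are seen.

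- **Estimator.** Kaplan–Meier risk in each arm at the chosen horizon, from randomisation, censoring at the final visit or the recorded last-contact date. The primary RR, with its confidence interval, is the ratio of the two risks.
- **Horizon.** Month 18 is reached by every completer and matches the sample size. If 24 months is kept, use the censored 24-month estimate and state that the sample size was based on 18 months.
- **Dating of cases.** Use adjudicated symptom onset where known, and apply one pre-stated rule in both arms to cases found only at the final examination. The rule should not count an examination finding from month 22 in an 18-month risk while excluding a symptomatic onset in month 22; that would mix horizons by mode of detection.
- **Sensitivity analysis.** PID through the final visit, including all cases.

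The cost is wording and a standard estimator, plus a real trade-off. Month 18 gives a shorter headline horizon with fewer events (control risk about 2.8% instead of 4.0% in the model above). Month 24 gives a less precise estimate near its end.

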#### Initial visit

Female students will be enrolled at each UHS for a period of 2 years. They may already be enrolled, or they may be new participants in the i-Share cohort (i.e., enrolled during the visit at which they will be offered to participate in both the i-Share cohort and the i-Predict trial).

Eligible participants will be approached by the physician investigator, provided information on the study and asked to sign an informed consent form if they agree to participate. They will be randomly allocated to the intervention or control group.

Participants will complete a baseline electronic self-administered questionnaire on their sexual and gynaecological history, use of hormonal contraception and condoms, and possible symptoms of infection. They will also provide a self-collected vaginal sample (month 0) on site.

Additionally, the following sociodemographic and medical data from the i-Share baseline questionnaire will be retrieved at baseline: type of training; year of registration; dwelling place; medical history; medical appointments; medication consumption; eating habits; well-being; and tobacco, alcohol and drug use.

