#### Randomisation

Block randomisation, stratified by participating university (Versailles Saint-Quentin-en-Yvelines, Bordeaux, Nice Sofia-Antipolis, Paris Sorbonne Universités, and Sorbonne Paris Cité), will be used to assign eligible participants who have provided informed consent to each group (1:1 ratio), resulting in one intervention group and one control group. Site-specific randomisation will be performed in the UHS of each of the five participating universities by the principal investigator at each site on the Cleanweb® electronic platform as soon as student recruitment is registered during the initial visit. Group assignment is generated at the same time as the participant’s study identification number; only principal investigators at each site and dedicated staff from the Centre National de Référence (French National Reference Centre for Chlamydial Infections) (CNR) have access to group assignment.

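### The primary RR is a crude ratio that ignores the university strata used in randomisation and does not use baseline Ct status: valid, but slightly inefficient and open to differential dropout

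*Protocol article*

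**What the plan says.** All of this is in the protocol article.

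- **Randomisation:** "Block randomisation, stratified by participating university", with allocation "to each group (1:1 ratio"). There are five universities.
- **Statistical analyses, primary:** the plan is to "estimate the RR of developing PID as the ratio of these incidences (intention-to-treat analysis"). Neither university nor any baseline variable is named in this estimator.
- **Statistical analyses, further:** "we will further stratify our RR analysis on baseline status of Ct infection". This is for comparison with previous trials and is not the primary estimate.
- **Statistical analyses, exploratory:** an "exploratory Cox regression analysis to adjust the RR of developing PID for other baseline characteristics of the participants". Imputation is considered for participant characteristics but not for Ct or PID status.
- **Initial visit:** "They will also provide a self-collected vaginal sample (month 0) on site", so the baseline swab is taken before any dropout.
- **Materials/laboratory analyses:** "Analysis will be deferred for the control group to after the 18-month study period", so control-arm baseline results exist by the time of analysis but not earlier.

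**The concern.** When allocation is balanced within strata, part of the outcome variation between strata can no longer enter the arm comparison. An analysis that ignores the strata still counts that variation in its standard error, so the interval is a little too wide and the test a little conservative.

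Baseline Ct status is different. It is not a stratification factor, so chance imbalance in it does add real variance to the crude RR. It is also the strongest predictor of PID in the sample size assumptions.

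The second issue is retention. Stratified blocks balance the arms at entry, not among women with a known outcome. The Sample size section allows for 10% attrition. Under Blinding, only intervention women with a positive result learn their allocation, so retention could depend on arm and Ct status jointly. PID work-up and final visits are also organised locally. A crude ratio among women with known outcome cannot correct for such patterns.

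**Working it through.** **Inputs.** From Sample size: 2000 per arm, 10% attrition (1800 evaluable), one-sided 5%, 80% power, RR 0.54. Baseline Ct prevalence and PID incidence in Ct-positives are 5% and 12% (scenario A) or 7% and 10% (scenario B). Ct incidence is 5% a year, PID in Ct-negatives 1% a year, and the lag 3 months. The 12% and 10% carry no time unit, and the control-arm risk is not stated.

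**1. The plan's own figure.** With RR 0.54 and the usual two-proportion formula, a control risk of 2.45% needs 1801 per arm, and 1801/0.9 gives 2002. That agrees with 2000, but the 2.45% is back-solved. The stated inputs over 18 months, read as yearly rates, give 2.61% (A) and 2.66% (B). The planned size is plausible but not independently confirmed. At 2.45% the primary analysis has about 1800 × (0.0245 + 0.54 × 0.0245) ≈ 68 events.

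**2. University.** The documents give no site-specific risks, so a spread is assumed. For five equal sites, the share of outcome variance explained is the between-site variance divided by p(1 − p). At overall risks of about 2 to 4%, a twofold range between lowest and highest site gives about 0.1 to 0.2%, and a fourfold range about 0.5 to 0.9%.

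**3. Baseline Ct.** Let π be the prevalence, p0 and p1 the arm risks, d0 and d1 the risk differences between Ct-positive and Ct-negative women within each arm, and n = 1800.

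- Crude variance of log RR: [(1 − p0)/p0 + (1 − p1)/p1]/n
- Reduction from standardising over Ct: π(1 − π)(d0/p0 + d1/p1)²/(2n)

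*(a) 12% read as yearly, treatment removes the excess risk (scenario A).* Control risk in Ct-positives is 1 − exp(−0.12 × 1.5) = 16.47%. In baseline Ct-negatives it is about 1.88%: roughly 1.5% background, plus PID from incident infections after the lag. So p0 = 0.05 × 0.1647 + 0.95 × 0.0188 = 2.61%. In the intervention arm the risk is about 1.54% in both strata, so d1 = 0.
- Crude variance: (37.3 + 63.9)/1800 = 0.0563
- Reduction: 0.0475 × (0.1459/0.0261)²/3600 = 0.00041, or 0.7%
- SE falls from about 0.237 to 0.236. Scenario B also gives 0.7%.

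*(b) 12% or 10% read as the risk over follow-up, RR 0.54 in both strata, Ct-negative risk 1.5 to 2%.* With 12% and 2%, p0 = 2.5% and d0/p0 = d1/p1 = 0.10/0.025 = 4.
- Reduction: 0.0475 × 8²/3600 = 0.00084 on 0.0623, or 1.4% (SE 0.2495 to 0.2478, power 79.5% to 80.0%)
- Over both scenarios and both Ct-negative risks, the range is 1.2 to 1.8%.

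*(c) 12% read as yearly and RR 0.54 in both strata.* Now d0/p0 = d1/p1 = 0.1459/0.0261 = 5.59.
- Reduction: 0.0475 × 11.18²/3600 = 0.00165 on 0.0596, or 2.8% (SE 0.244 to 0.241, power about 81.0% to 82.0%)
- This is the most favourable case. It sits badly with the plan's assumption of 100% treatment efficacy.

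Simulated trials under (a) and (b) give Mantel-Haenszel to crude variance ratios of 0.986 to 0.994, in line with the formula.

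**4. Dropout (retention figures assumed).**

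- *By arm and Ct:* take the risks in (c) and retain 70% of Ct-positive intervention women and 90% of everyone else. Intervention risk among completers is (0.05 × 0.7 × 0.0889 + 0.95 × 0.9 × 0.0102)/(0.035 + 0.855) ≈ 1.33%. The crude RR is about 0.51 instead of 0.54, a shift of about a quarter of one SE on the log scale. A Ct-standardised RR stays at 0.54. Under (a) there is no shift, because Ct-positive and Ct-negative intervention women have the same risk.
- *By arm and site:* one of five sites at 4.2%, the others at 2.45% (mean 2.8%), and retention at the high-risk site 80% in one arm and 90% elsewhere. That arm's risk is (0.8 × 4.2 + 3.6 × 2.45)/4.4 = 2.77%. The RR moves by about 1%, or 5% of one SE (about 0.24).

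**The case against.** The strongest reply is that nothing here is an error. The crude intention-to-treat RR is unbiased under this randomisation, ignoring strata errs on the conservative side, and stratified inference may be specified in an analysis plan that is not shown. That stands as a limit on the weight of the point. It does not remove it: the article states the primary estimator, and as stated that estimator leaves out the design factor.

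Several stronger readings are tempting, and the documents do not support them.

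- **That the RR is exposed to site imbalance.** Stratified 1:1 blocks already balance sites at entry. Only incomplete blocks and differential dropout remain.
- **That baseline Ct is ignored, or known for everyone.** A Ct-stratified RR is planned, though not as primary. The swab is collected from all, but control swabs are tested late and Ct status is excluded from imputation, so some results may be missing.
- **That Ct offers a large gain.** It explains a few per cent of control-arm outcome variance on the yearly reading, but that is not the precision of the RR. Contrasts such as 18% against 2% PID risk are not in the protocol; they rest on the yearly reading.
- **That the Cox model should be replaced.** It is exploratory. Final visits fall between months 18 and 24 and 10% attrition is expected, and Cox handles that censoring. At 2 to 3% risk the hazard ratio and RR nearly coincide. Only the label is inexact.

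**Conclusion.** The point holds as a minor alignment and efficiency matter. The primary RR does not reflect the stratification factor and uses the strongest available baseline predictor only in a further analysis. The primary conclusion is not threatened.

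The size is under 1% of variance for university, given assumed site spreads of up to fourfold. For baseline Ct it is about 0.7% in the case closest to the plan's own treatment assumption, 1.2 to 1.8% with a common RR and the incidence read as a follow-up risk, and about 2.8% at most. Power rises by no more than about one point.

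The protection against differential dropout may matter more than the precision, but it depends on retention patterns that the documents do not give. Standardisation removes the bias only if loss depends on nothing beyond arm and the adjusted variables.

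**What to change.** Amend the primary analysis statement along these lines:

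- Estimate the primary RR, its confidence interval and its test stratified by university, for example by Mantel-Haenszel or as a standardised marginal RR.
- Add baseline Ct as a standardisation covariate. Standardisation suits Ct better than Mantel-Haenszel weighting, because the effect may well differ between Ct-positive and Ct-negative women. With about 68 events, let university and Ct enter as main effects and do not cross-classify them.
- State a simple rule for missing baseline Ct, such as a missing category, and report missing counts by arm, since control swabs are tested later.
- Report the crude ratio as supportive, and keep the planned Ct-stratified results.
- Keep the exploratory Cox model and call its estimate a hazard ratio.

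The cost is a few sentences, written before control-arm results are available. No extra participants, samples or data are needed. If the analysis plan already does this, the article's description only needs to be brought into line.
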